### Statistical Analysis

Descriptive and inferential statistics will be used to characterize the study sample and test the hypotheses. Descriptive results for all quantitative variables such as age will be presented as mean (SD; for normally distributed data) or median with interquartile range (for data not normally distributed), while numbers (percentage) will be reported for all qualitative variables such as gender.

To assess the independent effect of CP transfusion safety and survival, we will conduct a PS-matching (based on age, gender, DM, HTN, and intubation) analysis. Among the predictors, exact matching will be enforced to achieve the balance for all predictors between the plasma and control groups.

The bivariate analysis will be performed using independent sample *t* test, Mann-Whitney *U* test, Pearson chi-square test, or Fisher exact test whenever appropriate to compare the demographic characteristics (eg, age, gender, nationality) and clinical characteristics (improvement in oxygenation, laboratory parameters, radiological findings, complications, and length of hospital stay) between those who will receive the CP and those who will not receive this therapy.

The multiple binary logistic regression model will be used to assess the effect of CP transfusion on 30-day mortality after adjusting for potential confounding factors compared to matched controls patients. The adjusted odds ratio and 95% confidence interval for the adjusted odds ratio will be reported. The Hosmer-Lemeshow goodness-of-fit statistics will be used to determine whether the model adequately describes the data.

The time-to-event analysis will be measured from the date of diagnosis. The overall survival at 30 days and 3 months will be evaluated using the Kaplan-Meier estimator and compared between the two groups (plasma recipients vs matched control patients) using the log-rank test. A Cox proportional hazard model will also be used to estimate the hazard ratio for in-hospital 30-day mortality for the plasma group compared with matched control group patients after adjusting for potential confounding factors. In addition, interactions between CP administration and all the predictors will be tested to see if the plasma effects will be the same in subgroups. A *P*<.05 (two-tailed) will be considered statistically significant. All statistical analyses will be performed using SPSS version 24 (IBM Corp).

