**Methods:**

Eligible patients with COVID-19 will be recruited for CP infusion according to the inclusion criteria. As COVID-19 has proven to be a moving target as far as its management is concerned, we will use current definitions according to the Ministry of Health (MOH) guidelines for diagnosis, treatment, and recovery. All CP recipients will receive supportive management including all available recommended therapies according to the available MOH guidelines. Eligible CP donors will be patients with COVID-19 who have fully recovered from their disease according to MOH recovery criteria as detailed in the inclusion criteria. CP donors have to qualify as blood donors according to MOH regulations except for the history of COVID-19 in the recent past. We will also test the CP donors for the presence of SARS-CoV-2 antibodies by a rapid test, and aliquots will be archived for future antibody titration. Due to the perceived benefit of CP, randomization was not considered. However, we will compare the outcome of the cohort treated with CP with those who did not receive CP due to a lack of consent or lack of availability. In this national collaborative study, there is a likelihood of not finding exactly matched control group patients. Hence, we plan to perform a propensity score matching of the CP recipients with the comparator group patients for the major characteristics. We plan to collect demographic, clinical, and laboratory characteristics of both groups and compare the outcomes. A total sample size of 575 patients, 115 CP recipients and 460 matched controls (1:4 ratio), will be sufficient to detect a clinically important hospital stay and 30-day mortality difference between the two groups with 80% power and a 5% level of significance.

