### Study Endpoint and Outcome Measures

Our primary endpoints are ICU (or designated area for critical patients) length of stay; safety of CP; and reporting of SAE such as anaphylaxis, TRALI, and TACO.

Our secondary endpoints will include number of days on mechanical ventilation, 30-day mortality, and days to clinical recovery as defined by the MOH.

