### Study Population

A total sample size of 575 patients, 115 CP recipients and 460 matched controls (1:4 ratio), will be sufficient to detect a clinically important difference of 11.6% between two groups (CP recipients vs matched controls) in 30-day mortality using a two-tailed *z* test of proportions and chi-square test with 80% power and a 5% level of significance. This 11.6% difference represents a 12.4% mortality in the CP recipient group and 24.4% mortality in the matched control patients [23].

The treatment group (CP recipients group) will have 115 patients who have COVID-19 but have not recovered yet as per the inclusion criteria. The control group (comparator group) will have 460 patients who are either not consenting to receive CP or those who will not be able to receive CP due to nonavailability to compare the efficacy of the CP. Control group patients will be subjected to propensity score (PS) matching based on age, gender, diabetes mellitus (DM), hypertension (HTN), and intubation.

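### Confounder-adjusted models are planned for 30-day mortality only; ICU stay, the primary efficacy endpoint, has no named analysis and hospital stay gets only unadjusted two-group tests

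*Protocol article*

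**What the plan says.** All references are to the protocol article.

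- **Design.** Abstract, Methods: "Due to the perceived benefit of CP, randomization was not considered". Controls are patients who did not consent to plasma or for whom none was available (Study Population).
- **Endpoints.** The section Study Endpoint and Outcome Measures begins as follows: "Our primary endpoints are ICU (or designated area for critical patients) length of stay; safety of CP; and reporting of SAE". The next sentence reads: "Our secondary endpoints will include number of days on mechanical ventilation, 30-day mortality, and days to clinical recovery". ICU stay is therefore the only efficacy measure among the primary endpoints, and mortality is secondary.
- **Matching.** Study Population: "Control group patients will be subjected to propensity score (PS) matching based on age, gender, diabetes mellitus (DM), hypertension (HTN), and intubation". Statistical Analysis opens its matching paragraph with "To assess the independent effect of CP transfusion safety and survival, we will conduct a PS-matching", lists the same five variables and adds that exact matching will be enforced on the predictors.
- **Unadjusted tests.** The bivariate paragraph lists t, Mann-Whitney, chi-square and Fisher tests for oxygenation, laboratory and radiological findings, complications and length of hospital stay, compared "between those who will receive the CP and those who will not receive this therapy".
- **Adjusted models.** The logistic model "will be used to assess the effect of CP transfusion on 30-day mortality after adjusting for potential confounding factors". The Cox model covers in-hospital 30-day mortality, also with adjustment. Both are described as comparisons with matched controls.

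**The concern.** The section assigns methods by outcome, and the assignment runs against the endpoint hierarchy. A secondary endpoint gets matching plus two covariate-adjusted models. The primary efficacy endpoint gets no named analysis, and its nearest relative, hospital stay, gets tests without covariates. By planning further adjustment for mortality, the investigators accept that a five-variable match may not be enough. The same reasoning applies to stay.

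Whether a patient becomes a recipient or a control depends on consent and plasma supply. The Discussion says that centres range from secondary to tertiary care with uneven experience, and that patients and physicians strongly believed in the treatment. Supply and length of stay could both plausibly vary by centre, and consent could vary with severity. Imbalance of that kind in factors outside the match would pass into an unadjusted result on stay. The stay and mortality results would also be adjusted for different things, which makes them hard to read together.

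**Working it through.** **1. What each outcome is given in Statistical Analysis**

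| Outcome | Endpoint status | Analysis named | Covariates | Described as matched in that sentence |
|---|---|---|---|---|
| ICU stay | primary | none | – | – |
| Hospital stay | not listed as an endpoint | bivariate tests | none | no |
| 30-day mortality | secondary | logistic regression | yes | yes |
| In-hospital 30-day mortality | secondary | Cox model | yes | yes |
| Survival to 30 days and 3 months | related to mortality | Kaplan-Meier, log-rank | none | yes |

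**2. Are the bivariate tests run on matched patients?** The bivariate sentence does not say so. Three other places suggest that they are:
- Study Population applies matching to the control group as such and calls the 460 matched controls.
- The abstract plans matching of the comparator group and presents the 115 + 460 matched sample as adequate for hospital stay as well as 30-day mortality.
- Interim Analysis uses 40 propensity-matched controls with a similar analysis.

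The likely reading is recipients against matched controls.

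**3. Group sizes.** These come from the mortality calculation in Study Population (1:4, 80% power, two-sided 5%). With a pooled z test, 12.8% against 24.4% (11.6 points) gives 115 + 460 = 575, the plan's figure. The printed rates, 12.4% and 24.4%, differ by 12.0 points and give 107 + 428 = 535 without continuity correction or 117 + 468 = 585 with it. That mismatch is a separate matter; 115 and 460 are used below as stated. The article gives no SD or target difference for stay.

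**4. Standard error of a difference in mean stay, in SD units** (normal approximation, equal SDs, matched sets ignored):

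SE = sqrt(1/115 + 1/460) = sqrt(0.008696 + 0.002174) = 0.104.

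Difference detectable with 80% power: (1.96 + 0.8416) × 0.104 = 0.29 SD.

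**5. Effect of leftover imbalance.** Suppose a prognostic score outside the match differs by d SD between groups and correlates rho with stay. With no treatment effect, mean stay then shifts by b = d × rho, and the test rejects with probability P(|Z + b/SE| > 1.96). Both d and rho are assumptions.

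| d | rho | b (SD) | b/SE | Rejection rate |
|---|---|---|---|---|
| 0 | – | 0 | 0 | 5% |
| 0.1 | 0.3 | 0.03 | 0.29 | 6% |
| 0.2 | 0.3 | 0.06 | 0.58 | 9% |
| 0.2 | 0.5 | 0.10 | 0.96 | 16% |
| 0.3 | 0.5 | 0.15 | 1.44 | 30% |

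The largest shift, 0.15 SD, is about half of the detectable difference (0.15/0.29 = 0.52).

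**The case against.** A reader might infer that matching is reserved for safety and survival, so that stay is compared crudely between unmatched groups and carries all the confounding of a non-randomised study. The documents do not support this. Matching defines the control group in Study Population, the abstract and Interim Analysis. If matching serves safety, the bivariate tests are the only named analysis that could carry a safety comparison, and hospital stay is in the same list. If the exact matching succeeds, the five variables are balanced, and adding them to a regression removes little further bias.

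A second tempting inference is that the 5% level fails for stay. That rests wholly on assumed imbalances: at the mild end the rate is 6%, which hardly matters. Imbalance in unmeasured factors would affect the mortality models too, and no regression removes it.

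It is also fair to say that a test on a matched sample is a recognised way to control confounding, and that an article may leave models for each outcome to a fuller document. This stands in part. But the article does more than omit detail. It states which outcome is adjusted, leaves the primary efficacy endpoint out of that list, and names hospital stay where the endpoint is ICU stay. The gap for measured factors outside the match remains on the favourable reading.

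**Conclusion.** The point holds in limited form. Adjusted models are specified for a secondary endpoint only. ICU stay has no named analysis, hospital stay has unadjusted tests, and the text is unclear on whether those tests use the matched set, though they probably do. What is left uncontrolled for stay is the part of confounding due to measured factors outside the five matching variables. Its size cannot be derived from the article. Under assumed shifts of 0.03 to 0.15 SD, the nominal 5% error would be about 6% to 30% at 115 against 460. Those figures illustrate sensitivity and do not predict what this trial would show. The change is worth making because it is cheap and gives the primary efficacy endpoint at least the protection already given to mortality.

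**What to change.** In Statistical Analysis:

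1. State that every comparison with controls, including the bivariate tests, uses the matched sample.
2. Name ICU length of stay and say how it will be analysed.
3. Make its main analysis a regression suited to skewed stay data (a proportional odds model is one option) with treatment group, the five matching variables and the same pre-specified baseline confounders as the mortality model. Name those confounders once, for all models. Candidates are illness duration, baseline oxygenation, APACHE and SOFA scores, and centre.
4. Do the same for days on mechanical ventilation and days to clinical recovery.
5. Keep the bivariate tests as description.

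**Cost.** One paragraph of wording, a few more model runs and some modelling assumptions; no extra patients. Illness duration and oxygen saturation are listed under Data Collection, and the severity scores under Response Assessment. That section describes follow-up after plasma, so it should be confirmed that the control forms record baseline scores. The adjustment reduces bias from measured factors only.

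### The length-of-stay, complication and log-rank comparisons ignore the 1:4 exactly matched sets, so they are modestly conservative if outcomes correlate within sets

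*Protocol article*

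**What the plan says.** Study Population sets the size as "A total sample size of 575 patients, 115 CP recipients and 460 matched controls (1:4 ratio"), justified by an unpaired z test of proportions and a chi-square test for 30-day mortality. The matching variables are age, gender, diabetes, hypertension and intubation. Statistical Analysis adds that "exact matching will be enforced to achieve the balance for all predictors between the plasma and control groups".

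The same section then names the tests:

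- **Group characteristics, laboratory and radiological findings, complications and length of hospital stay:** "The bivariate analysis will be performed using independent sample" t test, Mann-Whitney, Pearson chi-square or Fisher exact test. This sentence does not say whether the matched or the unmatched sample is used.
- **Survival:** Kaplan-Meier curves "compared between the two groups (plasma recipients vs matched control patients) using the log-rank test". Here the matched sample is explicit, and no stratification by set is stated.
- **30-day mortality:** ordinary multiple logistic regression and a Cox model, each adjusted for confounders that are not listed.

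Interim Analysis repeats a similar analysis on 40 recipients and 40 matched controls. No paired, conditional, set-stratified or cluster-robust method is named.

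**The concern.** Patients matched exactly on predictors of outcome should resemble each other in outcome. A test that treats the two groups as independent samples then charges the comparison with between-set variation that the matching has removed. The standard error is too large, the P value too large and the interval too wide.

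This matters most where the plan offers nothing else. ICU length of stay is a primary endpoint under Study Endpoint and Outcome Measures. The only test named for any length of stay is the bivariate one, and it names hospital stay. Complications are compared in the same way, and for harms an oversized standard error makes a real excess harder to see. The interim has few patients, and Time of the Study makes extension depend on whether it shows benefit.

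**Working it through.** **1. The plan's own figure.** Inputs from Study Population: two-sided 5%, 80% power, ratio 1:4, difference 11.6 points. With p1 = 0.128, p2 = 0.244 and pooled p = (0.128 + 4 × 0.244)/5 = 0.2208:

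n1 = [1.96 × √(0.2208 × 0.7792 × 1.25) + 0.8416 × √(0.128 × 0.872 + 0.244 × 0.756/4)]² / 0.116² = (0.909 + 0.334)² / 0.01346 ≈ 115.

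So 115 + 460 comes from an unpaired test at 80.1% power. The printed rates of 12.4% and 24.4% differ by 12.0 points and give 107; that discrepancy is a separate matter.

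**2. Variance with matched sets.** Let s² be the outcome variance and ρ the within-set correlation. For one recipient against the mean of four controls:

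Var = s² + (s²/4)(1 + 3ρ) − 2ρs² = 1.25 s²(1 − ρ).

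Over 115 sets this is 1.25 s²(1 − ρ)/115. The independent-samples variance is s²(1/115 + 1/460) = 1.25 s²/115. The matched variance is therefore (1 − ρ) times the one the planned tests use. At 1:1 with 40 pairs, 2s²(1 − ρ)/40 against 2s²/40 gives the same factor.

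**3. Continuous outcome (large-sample).** The protocol gives no ρ; 0.1 to 0.2 is an assumption. With the comparison sized for 80% under independence, the standardised effect is 1.96 + 0.84 = 2.80.

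- Type I error of the unpaired test = 2[1 − Φ(1.96/√(1 − ρ))]
- Power, unpaired = Φ(0.84/√(1 − ρ))
- Power, matched = Φ(2.80/√(1 − ρ) − 1.96)

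| ρ | SE ratio 1/√(1 − ρ) | Type I, unpaired | Power, unpaired | Power, matched |
|---|---|---|---|---|
| 0 | 1.00 | 5.0% | 80.0% | 80.0% |
| 0.1 | 1.05 | 3.9% | 81.3% | 84.0% |
| 0.2 | 1.12 | 2.8% | 82.7% | 88.0% |

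**4. Binary outcome (simulation).** 115 sets of 1:4, 20,000 runs per row. Null: 24.4% in both groups. Alternative: 12.4% against 24.4%. The matched test is Mantel-Haenszel stratified by set.

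| ρ | Type I, chi-square | Type I, stratified | 95% CI coverage, unpaired (null) | Power, chi-square | Power, stratified |
|---|---|---|---|---|---|
| 0 | 4.8% | 4.7% | 94.9% | 83.8% | 83.6% |
| 0.04 | 4.5% | 4.8% | 95.3% | 84.5% | 85.3% |
| 0.15 | 3.5% | 5.2% | 96.2% | 85.1% | 88.4% |
| 0.26 | 2.4% | 4.9% | 97.5% | 86.3% | 92.4% |

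A second simulation gave 3.5% and 2.8% at ρ = 0.10 and 0.19 for a binary outcome, and 4.1% and 3.0% at 0.1 and 0.2 for a continuous one. The log-rank test was not simulated. Its variance also assumes independent patients, so the direction is the same.

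**5. Adjusted logistic regression.** A simulation of 1,500 runs, with five exactly matched covariates all in the model and ordinary standard errors, gave type I error 5.5% (Monte Carlo SE 0.6 points) and coverage of 94.5% under the null and 95.6% under the alternative. Power was 85.5%, against 81.7% for the crude chi-square test. Adjusting for the matching variables recovers what the unpaired test gives away.

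**The case against.** The strongest reply is that the error is on the safe side and the trial was sized on the same unpaired test. That stands. A reader might infer from unmatched tests on matched data that false positives are inflated or that the trial is underpowered. Neither follows: with positive correlation the type I error falls below 5%, and the power of the unpaired test stays at or above 80% in every scenario examined.

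A second reply is that 30-day mortality is assigned to adjusted models, not to a crude chi-square test. This also stands. One might infer that the logistic and Cox results are invalid too. If the five matching variables are among the covariates, the logistic check shows ordinary inference close to nominal, and the same reasoning applies to Cox. Since the covariates are unlisted, this can be neither confirmed nor ruled out.

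Third, the bivariate sentence may describe the unmatched cohort, for which independent-sample tests are the right form. This is a fair reading. But then the only named length-of-stay comparison in a non-randomised study would use neither matching nor adjustment. The log-rank sentence has no such ambiguity.

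Two further inferences go beyond the text. Reuse of controls could reverse the direction of the error, but the protocol mentions no matching with replacement and plans for 460 control patients. A larger power loss appears if the pooled chi-square is set against a set-based test with unpooled variance, but most of that gap is present at zero correlation and is not due to matching.

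**Conclusion.** The point holds in limited form. For length of stay and complications (if compared in the matched sample) and for the log-rank test, the named analyses ignore the matched sets. At an assumed within-set correlation of 0.1 to 0.2, true type I error is about 3-4%, standard errors are about 5-12% too large, and about 2-5 points of power are given up against a like-for-like matched test. All of this rests on the assumed correlation. It is plausible because the matching variables are presumably prognostic, but the protocol gives no value, and at zero correlation the effect vanishes.

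This is a stated choice of test, not a detail left for later, so a statistical analysis plan would have to override it. It is worth correcting because it touches a primary endpoint and the interim. It does not threaten the validity of a positive result.

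**What to change.** State in Statistical Analysis which sample the bivariate comparisons use. For the matched sample, state that length of stay, complications and survival are compared with standard errors clustered on the matched set, or with models adjusted for age, gender, diabetes, hypertension and intubation. State that the logistic and Cox models include those five variables or use set-clustered standard errors. Apply the same rule to the 40:40 interim.

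The cost is analysis wording only: no new data and no change in sample size. The set identifier must be kept in the dataset if clustering is used; the adjustment route needs only ordinary regression on variables already collected for the matching.

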### Data Collection

Clinical information of all enrolled patients will be retrieved from the hospital electronic or paper records system, including the following:

Baseline demographic dataDays of illness durationPresenting symptomsRadiological findings (chest x-ray and computed tomography [CT] scan chest, if possible) on the day of hospital admission; on the day of ICU admission; on the day of CP infusion (day 0); and on days 3, 7, 14, and 30Laboratory infectious marker testing results like respiratory, urinary, or blood cultureLaboratory inflammatory markers: CRP (day of CP infusion [day 0] and then on days 3, 7, 14, and 30)Application of assisted mechanical ventilation and their modes, intranasal oxygen inhalation, number of days of intubation, or nasal oxygen supportMedication regimen (eg, hydroxychloroquine, azithromycin, any antiviral therapies, steroids, tocilizumab)Complications including acute renal failure, acute coronary syndrome, myocarditis, ARDS, gastrointestinal complication, and nosocomial infectionThe SARS-CoV-2 RNA from the serum sample will be monitored during treatment and at day 14 of recovery or discharge, whichever is later.

We plan to test for all of the following parameters for patients with COVID-19:

Complete blood count (CBC) differential to include percent and ALC, and percent and absolute neutrophil countChemistry panel to include total protein, albumin, lactate dehydrogenase, alanine aminotransferase and aspartate aminotransferase, and procalcitoninCardiac biomarkers (eg, cardiac troponins)Creatine phosphokinaseFerritinFull coagulation profile to include partial thromboplastin (PT), activated PT time, fibrinogen, and D-dimerCRPOxygen saturationRadiological examinationABO RhD grouping and antibody screeningrRT-PCR test for SARS-CoV-2Test for IgG and IgM antibodies against SARS-CoV-2

CP donors will essentially undergo routine blood donation processes such as donor history questionnaire, clinical examination, and testing for the infectious marker (serology and nucleic acid testing methods) along with ABO RhD grouping, antibody screening, and CBC. They will also undergo a test for IgG and IgM antibodies against SARS-CoV-2, which should be positive for IgG.

Data collection forms have been developed to collect data for CP donors, recipients, and controls (comparators).

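### Oxygenation, laboratory and imaging results are compared by tests that do not adjust for the marker's own baseline, in non-randomised groups not matched on it

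*Protocol article*

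**What the plan says.** All references are to the protocol article.

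- **Tests.** Statistical Analysis lists the independent t test and the Mann-Whitney test, and continues with "Pearson chi-square test, or Fisher exact test whenever appropriate to compare the demographic characteristics" and then "clinical characteristics (improvement in oxygenation, laboratory parameters, radiological findings, complications, and length of hospital stay) between those who will receive the CP" and patients who do not receive it. The sentence does not say that the comparison is limited to matched patients.
- **Adjusted models.** The logistic model "will be used to assess the effect of CP transfusion on 30-day mortality after adjusting for potential confounding factors". The Cox model will "estimate the hazard ratio for in-hospital 30-day mortality for the plasma group compared with matched control group patients after adjusting for potential confounding factors". No adjusted model is named for any other outcome.
- **Allocation and matching.** Under Study Population, controls are "patients who are either not consenting to receive CP or those who will not be able to receive CP due to nonavailability". They undergo "propensity score (PS) matching based on age, gender, diabetes mellitus (DM), hypertension (HTN), and intubation". Statistical Analysis adds that exact matching on these predictors will be enforced.
- **Values collected.** Data Collection schedules "CRP (day of CP infusion [day 0] and then on days 3, 7, 14, and 30", and imaging on the same days as well as at hospital and ICU admission. Oxygen saturation is listed there and again under Response Assessment.
- **Status.** Study Endpoint and Outcome Measures does not list oxygenation, laboratory values or imaging as primary or secondary endpoints.

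**The concern.** Recipients and controls are not randomised, so they may differ in CRP, oxygenation or lung involvement at the start. Matching on age, gender, two comorbidities and intubation need not remove such a difference, and the tests named cannot adjust for it.

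What happens next depends on the quantity tested. In a change score, a group that starts worse tends to show more improvement if both groups drift towards the same mean. In a comparison of follow-up values, that group still looks worse, because part of the starting difference remains. The text speaks of improvement, at least for oxygenation, but does not say whether laboratory and imaging results are analysed as change or as follow-up values. The possible error therefore has no fixed sign.

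The Introduction expects plasma to improve clinical, laboratory and radiological features, so these comparisons are likely to be read as evidence of efficacy. The Interim Analysis section repeats a similar analysis at 40 versus 40. Time of the Study makes extension depend on an interim benefit without naming the outcome, so marker results are not excluded from that decision.

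**Working it through.** **The plan's own figure.** The only design calculation is for 30-day mortality. A two-sided 5% pooled z test with 80% power and a 1:4 ratio gives 115 + 460 = 575 for 12.8% versus 24.4%, which is the stated 11.6-point difference. The printed 12.4% versus 24.4% is a 12.0-point difference and gives 107 + 428 = 535. That mismatch is a separate matter. Only the group sizes of 115 and 460 are used below.

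**Inputs from the article.** n = 115 and 460; two-sided 5% level.

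**Assumptions.** The article gives no SD, correlation or baseline difference for any marker. Assume SD 1 at baseline and follow-up, correlation r = 0.3, 0.5 or 0.7, recipients d = 0.3 SD worse at baseline, no plasma effect, and the same regression on baseline in both groups (regression to a common mean).

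**Formulas.** Let k = √(1/115 + 1/460) = 0.1043.

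- Change score: bias (1 − r)d towards benefit; SE = k√(2(1 − r)).
- Follow-up value: bias rd towards harm; SE = k.
- Baseline-adjusted: bias 0; variance factor 1 − r².
- Rejection rate: 1 − Φ(1.96 − |bias|/SE) + Φ(−1.96 − |bias|/SE).

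| r | Change: bias / SE | Falsely significant | Follow-up: bias / SE | Falsely significant |
|---|---|---|---|---|
| 0.3 | +0.21 / 0.1234 | 39.8% | −0.09 / 0.1043 | 13.9% |
| 0.5 | +0.15 / 0.1043 | 30.1% | −0.15 / 0.1043 | 30.1% |
| 0.7 | +0.09 / 0.0808 | 20.0% | −0.21 / 0.1043 | 52.2% |

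A simulation of 4,000 trials at r = 0.5 and d = 0.3 gave 30.9% for change, 30.1% for follow-up and 4.7% for the baseline-adjusted regression.

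**Sensitivity to d.** For d from 0.2 to 0.5 SD over the same r, the change-score rate runs from 11.5% to 81.0% at 115 versus 460, and from 6.4% to 26.3% at the 40 versus 40 interim.

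**If the group difference is stable.** Suppose the gap d persists unchanged and plasma has no effect. The change score then has bias d − d = 0. The adjusted regression leaves −d + rd = −(1 − r)d, that is −0.21 to −0.09 SD at d = 0.3. The choice between the two analyses therefore rests on an assumption that the article's data cannot settle in advance.

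**Precision with equal baselines.** The variance ratio of adjusted to change score is (1 − r²)/(2(1 − r)) = (1 + r)/2 = 0.65, 0.75, 0.85. The change-score test needs 1/0.65 = 1.54 to 1/0.85 = 1.18 times as many patients. Against the follow-up-only test the factor is 1/(1 − r²) = 1.10, 1.33, 1.96.

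**The case against.** **Status of the markers.** They are not listed endpoints, and the trial's mortality models are adjusted. This stands: the point does not reach the ICU-stay, safety or mortality conclusions. Covariate detail for supportive measures is also often left to an analysis plan, which is not shown here. Against that, the article does not stay silent. It names the tests, and those tests exclude a covariate.

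**Baseline is already used.** A reader might infer that the patient's own starting value is ignored altogether. The text does not support that, because improvement implies a comparison with an earlier value, at least for oxygenation. What can be said is that baseline is never a covariate. Starting worse and seeming to improve more is an artefact of a change score, which does use baseline. Without baseline, the same group would look worse.

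**Bias is not demonstrated.** A reader might also infer that plasma will be falsely credited. The article gives neither the size nor the direction of any imbalance, and with a stable group difference the change score is free of this bias. This objection stands, and it is why the figures are conditional and why a change-score analysis belongs beside the adjusted one.

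**Balance is partly achieved.** Intubation is matched, and eligibility restricts severity. Both narrow the possible gap in oxygenation. They say little about CRP or imaging within the severe group.

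**The repair is not free.** Day 0 is the day of plasma infusion, so controls have no stated day 0. No imaging grade is described, and CT is taken only where possible. This stands and limits the fix.

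**Conclusion.** The point holds in a limited form. The article fixes unadjusted two-sample tests for oxygenation, laboratory and imaging results in non-randomised groups that are not matched on those markers, and reserves covariate adjustment for 30-day mortality.

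The gain in precision from adjustment when baselines are equal depends only on r: 65% to 85% of the change-score variance for r = 0.3 to 0.7. The bias is conditional. The false-positive rates of about 40% to 20% (change) and 14% to 52% (follow-up) rest on an assumed 0.3 SD imbalance and on regression to a common mean. The article neither shows nor rules out either assumption. The consequence is confined to supportive measures, unless they are used to judge interim benefit.

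**What to change.** In Statistical Analysis, take oxygenation and continuous laboratory markers such as CRP out of the two-sample tests. For each marker:

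1. Regress the follow-up value on group with the same marker's baseline value as covariate, in the matched sample.
2. Report the adjusted difference with its 95% confidence interval.
3. Report a change-score analysis as sensitivity, since the two analyses rest on different assumptions about how the groups differ.
4. Take the control baseline on a defined day comparable with day 0.

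For imaging, use an ordinal regression with the baseline reading as covariate only where graded baseline and follow-up readings exist. Describe the results as supportive.

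A model for CRP across all visits to day 30 is better not adopted by default, because it would also need a stated rule for patients who die before the later visits.

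**Cost.** A few sentences in the analysis section and a definition of the control baseline day. No new type of measurement is needed for CRP or oxygen saturation, but control values must be extracted for the chosen day. Patients without a recorded baseline need imputation or drop out of that marker's analysis.
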